#### Assessing outcome 2: feasibility of simplified and same-day care models

A primary study aim (aim 2) is to assess and compare the feasibility of implementing a simplified care model versus same-day test and treat model within primary/secondary health services and harm reduction settings.

Feasibility of implementation will be assessed based on retention in care numbers and complemented by the effectiveness outcomes, including treatment uptake and SVR outcomes. Descriptive statistics will be used to calculate the proportion of participants progressing through the cascade of care, including proportion of participants who test antibody positive and then RNA positive for hepatitis C, and the proportion who then commence on treatment in the simplified model of care (arm 1) and in the same-day treatment model (arm 2).

In addition, feasibility and implementation requirements, and broader implementation and scalability considerations, will be assessed through a mixed-methods process evaluation (described below). The updated Consolidated Framework for Implementation Research (CFIR) by Damschroder *et al*^46^ and the recommended adaptations for LMICs by Means *et al*^47^ will be used to develop the data collection tools and analysis framework to guide the feasibility assessment. Data will be drawn from the process activity logs, monitoring visits and meetings, reflections and learning workshops and key informant interviews. For comparison across the sites, the implementation of the models of care at each site will be described following the Template for intervention description and replication (TIDieR) checklist and guide^48^ to provide a standardised description of study implementation.

This will contribute to an assessment of whether the model of care was implemented with fidelity and if effectiveness outcomes can be effectively replicated, providing evidence for the potential successful scale-up.

Primary research question #3: What is the comparative cost-effectiveness between the same-day treatment initiation model (arm 2) and the simplified care model (arm 1)?

#### Assessing outcome 3: comparative cost-effectiveness of same-day model versus simplified model (arm 2 vs arm 1)

A mathematical model will be used to estimate average hepatitis C-related costs and quality-adjusted life years per person for a theoretical cohort of 100 people in each country under three scenarios: (1) no treatment; (2) the simplified care model and (3) the same-day treatment model. Prevalence of hepatitis C antibodies and RNA in each country will be based on study data. The effect of the different models (arm 1 simplified care model and arm 2 same-day treatment model) on linkage to care and treatment uptake will be based on the pooled study outcomes across countries, and costs calculated using a decision tree structure capturing the cascade of care. The average country-specific cost per person in each scenario will be estimated from study data, using a health systems perspective (ie, consumables, medicines, health provider time and other costs identified by project staff as relevant for intervention delivery) and a societal perspective (ie, also including lost productivity among people with hepatitis C). For each country, health-related quality of life weights will be estimated using data from the EQ-5D-5L tool in each country. The incremental cost-effectiveness ratio (difference in cost divided by difference in quality-adjusted life years) will be calculated for the simplified care scenario compared with the no treatment scenario, and for the same-day treatment scenario compared with the simplified care scenario.

Estimates of average cost per person and treatment uptake for the simplified care and same-day treatment models (including the cost of the participants overtreated) in each country will be used as inputs to a national dynamic transmission model, which will be used to estimate the potential population-level benefits of scaling up each model of care.

#### Assessing secondary outcomes

##### Impact of same-day treatment initiation model on treatment completion and cure

Participants will be classified as completing treatment if they self-report that they have taken at least 8 weeks of treatment, with <14 days missed doses. Proportion completing treatment will be assessed among those who were confirmed RNA positive. The proportion of participants who complete hepatitis C treatment will be compared between arms. We will also assess treatment completion based on completion of the full 12-week treatment course.

The proportion of participants who achieve SVR (4–20 weeks post-treatment completion) among those who were confirmed RNA positive and initiated hepatitis C treatment in the simplified care model (arm 1) will be compared with the same-day treatment care model (arm 2), using per-protocol analysis of those allocated to each arm.

##### Time to initiate treatment

The time from HCV antibody RDT to prescription and dispensing of first 4 weeks of DAAs, and to self-report taking first tablet of treatment will be calculated, and compared across arms. These will be calculated both among those who were HCV antibody positive (arm 2) and also among those confirmed RNA positive (arms 1 and 2) and initiated hepatitis C treatment.

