### Trial study design

This paper describes the study protocol for a multicountry non-randomised, quasi-experimental, prospective comparative two-arm trial to assess the feasibility of implementation, retention in hepatitis C care and achievement of cure and cost-effectiveness outcomes, comparing two simplified hepatitis C testing and treatment pathways.

Arm 1 is a standardised simplified test and treat model of care following global guidance, and arm 2 is an innovative rapid, same-day treatment initiation using a presumptive treatment approach based on shortened read-time of the POC OraQuick hepatitis C antibody test result.^23^

Responding to WHO’s call for further simplification and decentralisation of hepatitis C testing and treatment, this study will be conducted in three LMICs, the Republic of Armenia (here, Armenia), Georgia and United Republic of Tanzania (herein, Tanzania), providing much-needed evidence from LMIC settings to increase access to hepatitis C treatment. In particular, this study is exploring opportunities to pursue a simplified and, ideally, one-step diagnostic algorithm, which is broadly recognised as a potentially major game-changer in HCV care.

All three countries have varied hepatitis C and injecting drug use epidemiology, harm reduction programming and national responses to hepatitis C. Georgia has a national decentralised hepatitis C programme, Armenia has a centralised programme only available in Yerevan, Tanzania has yet to implement a national programme. Given all three countries are in a distinct phase of their national response to hepatitis C, implementing the trial in these environments will provide insights into its feasibility and utility in each setting and allow for greater applicability of findings globally.

Participants will be consecutively enrolled into arm 1 (standardised simplified model of care), until the study’s country-level treatment initiation target is met. Then, participants will be consecutively enrolled into arm 2 (same-day treatment initiation), until the study’s country-level treatment initiation target has been met. Enrolment will close when arm 2 reaches country-level treatment initiation targets.

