### Study outcomes

The three primary research questions and outcomes are:

Does the same-day treatment initiation model (arm 2) increase hepatitis C treatment uptake and achievement of SVR (cure) among people who inject drugs compared with the simplified care model (arm 1)?What is the feasibility of implementing a decentralised hepatitis C simplified care model (arm 1) and the same-day treatment care model (arm 2) in the varied healthcare settings in the three study countries (Armenia, Georgia and Tanzania)?What is the comparative cost-effectiveness between the same-day treatment initiation model (arm 2) and the simplified care model (arm 1)?

The secondary research questions and outcomes pertain to the acceptability of the two care models to participants, to healthcare practitioners including the barriers and enablers to support scale-up of these models in country. Additional secondary outcomes include:

the time to treatment initiation and the proportion completing treatment;the test performance (sensitivity, specificity, positive predictive values and negative predictive values) of the 5 min read-time OraQuick HCV antibody result in identifying participants with viraemia from those without viraemia;the optimal ‘cut-off’ read-time to identify participants with viraemia (using arm 1 and arm 2 data) to reduce the proportion of participants without viraemia who are ‘overtreated’ for hepatitis C in the same-day treatment initiation model of care;comparison of the care cascade for both arms 1 and 2 with available historical data, where feasible, including the proportion of people who inject drugs reached through the models.

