#### Superiority of ‘same-day initiation’ (arm 2) versus ‘simplified care pathway’ (arm 1)

Acknowledging there are considerable uncertainties around expected uptake of DAAs in both arms, we examined the required sample size in various scenarios of treatment uptake where the intervention (arm 2) would be 5%–10% superior to the simplified care (arm 1). A sample of 700 (350 in each arm) would enable a minimum effect size of 7% favouring arm 2 (presuming 85% uptake in arm 1 simplified care arm) to be detected with 80% power at the 5% significance level. We have assumed 85% treatment initiation based on previous studies that have implemented simplified care pathways in LMIC settings,^17^ accounting for a 15% loss to follow-up prior to treatment initiation. We expect cure rates to be equal across both arms (~95%).

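### Time to treatment initiation is compared between arms only among RNA-positive participants who started, so the comparison is selective and its bias has no fixed direction

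*Protocol article*

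**What the plan says.** The protocol article lists "the time to treatment initiation and the proportion completing treatment" among its additional secondary outcomes (Study outcomes). Under Time to initiate treatment, two intervals are defined, both starting at the antibody rapid test. One ends at prescription and dispensing of the first four weeks of drug. The other runs "to self-report taking first tablet of treatment will be calculated, and compared across arms".

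That section names two analysis sets. The first is those "among those who were HCV antibody positive (arm 2", with arm 2 alone in the brackets. The second is "also among those confirmed RNA positive (arms 1 and 2) and initiated hepatitis C treatment". No set is named that covers both arms and keeps RNA-positive people who never start. If the requirement of having initiated is read as applying to the first set too, this does not change.

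The sample size section (Superiority of same-day initiation versus simplified care pathway) gives the only figures on non-starting. It works from "presuming 85% uptake in arm 1 simplified care arm", "accounting for a 15% loss to follow-up prior to treatment initiation". It also says that 350 per arm "would enable a minimum effect size of 7% favouring arm 2".

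**The concern.** Whether a participant starts treatment is decided after enrolment, and raising that proportion is the purpose of arm 2. Restricting the time comparison to starters therefore conditions on something the intervention affects. RNA-positive people who never start have the longest time without treatment, yet they disappear from the comparison, and in different proportions by arm if uptake differs.

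At stake is the interpretation of the secondary outcome closest to what same-day treatment sets out to do. In arm 1 treatment starts at the second visit; in arm 2 it starts at the baseline visit for those eligible (Intervention). Among starters the contrast is therefore largely set by the design. It does not show how much sooner a person with viraemia gets onto treatment under one pathway than under the other. A reader also cannot correct the starters-only figure, because the sign of the error depends on the uptake in each arm and on the summary used.

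The article does not impose this restriction on treatment completion, which it assesses among all confirmed RNA positives (Impact of same-day treatment initiation model on treatment completion and cure).

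**Working it through.** **Inputs from the article.** Arm 1 uptake is 85%, so 15% never start. The detectable difference is 7 points, so the alternative for arm 2 is 92% uptake and 8% never starting. The equivalence scenario has equal uptake between 75% and 95%. There are 350 participants per arm, with 80% power at the 5% level.

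**The plan's own figure.** For 85% versus 92%, two-sided 5% (sidedness is not stated) and 80% power, the two-proportion formula gives 325 per arm without continuity correction and 353 with it. The stated 350 is reproduced to within 1%, which supports reading the 7-point effect as 85% versus 92%. Power at 350 per arm is 82.9% without the correction. The article gives no figure for time to initiation.

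**Assumptions, because the article gives no start-time distribution.** Arm 2 starters begin on day 0. Arm 1 starters' times are log-normal with median 7, 14 or 21 days and log-SD 0.6. The horizon H is 84 days.

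**Formula.** Let u1 and u2 be uptake and m the arm 1 starters' mean delay, capped at H. A never-starter contributes H days.

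- Starters only: difference = m − 0 = m.
- All RNA positives: difference = [u1·m + (1 − u1)·H] − (1 − u2)·H = u1·m + (u2 − u1)·H.
- Understatement by the starters-only analysis = (u2 − u1)·H − (1 − u1)·m.

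At 85% versus 92% this is 0.07 × 84 − 0.15m = 5.88 − 0.15m days. It reaches zero at m = 5.88 / 0.15 = 39.2 days, and beyond that the starters-only figure is an overstatement.

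| Arm 1 median (assumed) | m to day 84 | All RNA positives, 85% vs 92% | Understated by | All RNA positives, 85% vs 85% | Overstated by |
|---|---|---|---|---|---|
| 7 days | 8.4 | 13.0 | 4.6 | 7.1 | 1.3 |
| 14 days | 16.7 | 20.1 | 3.4 | 14.2 | 2.5 |
| 21 days | 24.9 | 27.1 | 2.1 | 21.2 | 3.7 |

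With equal uptake the first term vanishes and the starters-only figure is too large by (1 − u1)·m. At a median of 14 days that is 0.25 × 16.7 = 4.2 days at 75% uptake and 0.05 × 16.7 = 0.8 days at 95%.

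**Other summaries, arm 1 median 14 days, 85% versus 92%.**

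- Median: arm 2's median is day 0 in either set. Over all RNA positives, arm 1's median is the 0.5 / 0.85 = 58.8th percentile of starters' times, which is 16.0 days. The difference is 14.0 days among starters and 16.0 among all, so it is understated.
- Share started by day 28: 87.6% of arm 1 starters have begun. Starters only: 100 − 87.6 = 12.4 points. All: 92 − 0.85 × 87.6 = 17.5 points. Understated.
- Share started on day 0: 100 points among starters, 92 among all. Overstated.
- Restricted mean to 28 days: 15.4 days among starters; 0.85 × 15.4 + 0.07 × 28 = 15.0 among all. Slightly overstated.

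The same selection therefore produces errors of either sign, depending on the summary, the horizon and the uptake in each arm.

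**The case against.** The strongest reply is that non-starters are not lost to the trial. Starting or not starting is the primary uptake outcome, and the care cascade reports the proportion who commence in each arm. Uptake plus delay among starters is a common two-part description. Time to initiation is one secondary outcome with no decision rule attached, and the full analysis plan may choose the summary measure. This limits the importance of the point but does not remove it. The article itself fixes the population for the comparison, and a separate uptake figure does not repair a time contrast made between differently selected groups.

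Four stronger readings are tempting and are not supported.

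- A reader might infer that the plan necessarily understates the benefit of arm 2. The calculations show reversals, including under the equal-uptake scenario the article itself plans for.
- A reader might put the hidden difference at about 6 days, from 0.15 × 84 − 0.08 × 84 = 12.6 − 6.7 = 5.9. That adds the never-starters' days without reducing the starters' weight; the term −0.15m must be included.
- A reader might say the plan expects 8% never starting in arm 2. Only the arm 1 figure is an assumption. The 92% is a detectable alternative, in a section that stresses uncertainty about uptake in both arms.
- A reader might worry about people not yet started when data close. The design section says "Enrolment will close when arm 2 reaches country-level treatment initiation targets", but the Project timeline section allows at least six months of follow-up after enrolment, so this group should be small.

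**Conclusion.** The point holds in a limited form. The only between-arm set for time to initiation is conditioned on having started, which the intervention is meant to change, so the comparison is selective. The direction of the bias is not fixed. If arm 2 raises uptake, understatement is likely for the median and the longer-horizon restricted mean. Overstatement is possible for the day-0 share, for short horizons, or when uptake is equal.

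At 85% versus 92%, the 84-day restricted mean difference is understated by about 2 to 5 days for assumed arm 1 medians of 7 to 21 days. This rests on the assumed start-time distribution and on all arm 2 starters beginning on day 0. Confidence is high that the set is conditioned on starting and moderate on the direction. The priority is modest.

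**What to change.** For the between-arm comparison, use all confirmed RNA-positive participants in both arms, under the same per-protocol arm definition as the primary analysis, with time counted from the date of the antibody test. RNA status comes from blood taken at visit 1 in both arms, so the set can be formed without reference to starting.

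Count known never-starters, and those lost before starting, as not started through day 84. Censor only where data end early for administrative reasons. Censoring at study exit would not do: the Study exit section lets exit follow about three weeks of failed contact, so such censoring would be informative and would largely bring the selection back.

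Report the cumulative proportion started at fixed days, for example 0, 7, 28 and 84, and the difference in restricted mean time to 84 days. Keep the starters-only summary and the arm 2 antibody-positive set, both labelled descriptive.

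The cost is a change of wording in the analysis plan for one secondary outcome, with no additional participants or visits. It relies on antibody test and first-dose dates, which the planned outcome already needs, and on start status for every RNA-positive participant, which the primary uptake outcome already needs.

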##### Accuracy of the shortened read-time of the HCV RDT

The test performance will be determined by calculating the sensitivity and specificity of the shortened 5 min read-time result, and the positive predictive values and negative predictive values. The proportion of participants with concordant results from the OraQuick rapid hepatitis C antibody test at the shortened 5 min read-time and from the confirmatory hepatitis C RNA test result will be calculated using data from both arms. Where data are available, we will also assess the performance characteristics of the rapid test by HIV status.

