#### Arm 1 study procedures

##### Visit 1: enrolment, laboratory investigations, physical examination and medical history taking

Eligible participants enrolled in the study will have a OraQuick rapid hepatitis C antibody test using a fingerstick specimen, according to the manufacturer’s instructions, with the result documented at 20 minutes. In addition, the OraQuick rapid test result for the first 5 min will be documented at 1 min intervals, including with a photograph to record whether the test is reactive or non-reactive at that time point. The exact time at which the test first turns reactive will also be recorded. The result at 20 min will be provided to the participant. If the antibody result is negative, confirmatory testing will not be offered and the participant will exit the study with no further investigations performed. If the antibody result is positive, blood samples will be collected for confirmatory laboratory RNA testing and additional pretreatment investigations including complete blood count (platelets, haemoglobin), liver function tests (alanine aminotransferase (ALT), aspartate aminotransferase (AST), albumin, bilirubin) and renal function tests (serum creatinine±estimated glomerular filtration rate (eGFR)). The FIB-4 score will be calculated and used to determine cirrhosis status.

In addition, additional rapid tests will be conducted at baseline visit:

HIV antibody 1/2 RDT using venous blood sample.Hepatitis B surface antigen (HBsAg) RDT using venous blood sample.Urine dip-stick pregnancy test for all female participants with childbearing potential aged 18–49 years (pregnancy test can also be completed as part of pretreatment laboratory investigations in arm 1).

The brands of HIV and HBsAg RDTs will be included in online supplemental material 1; brands differ by country, depending on national procurement.

In Tanzania and Armenia, those who return a non-reactive HBsAg RDT and have no evidence of prior hepatitis B vaccination will be offered vaccination through the study. Evidence of vaccination is sourced through medical records accessible by study sites. In Georgia, those eligible for vaccination will be referred to a newly established national programme for vaccination.

Those newly diagnosed with HIV will be referred to treatment and be allowed to represent for study participation once their HIV is clinically stable, if recruitment is still open at that time in Armenia and Tanzania.

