### Arm 2 study procedures

#### Visit 1: enrolment, laboratory investigations, physical examination, medical history taking, drug-drug interactions review and presumptive treatment prescription

Eligible participants enrolled in arm 2 will undergo an OraQuick rapid hepatitis C antibody test using a fingerstick specimen as per arm 1. The result at 5 min will be provided to the participant as a preliminary result and used to inform whether same-day treatment is offered. This is the key difference between arm 1 and arm 2, with participants in arm 2 offered presumptive treatment based on this result at 5 min, without waiting for the RNA result.

Laboratory testing on a venous sample is then required to confirm whether the participant has current infection. If the antibody result is negative, confirmatory testing will not be offered and the participant will exit the study with no further investigations performed (as per arm 1).

If the antibody result is positive, blood samples will be collected for confirmatory laboratory RNA testing and additional investigations (as per arm 1). The FIB-4 score will be calculated and used to determine cirrhosis status.

If the POC result is positive at 5 min, blood samples will be collected for confirmatory laboratory RNA testing and additional investigations. Additional rapid tests, including HIV antibody 1/2 RDT, HBsAg RDT, rapid urine pregnancy tests, physical examination for signs and symptoms of decompensated cirrhosis, medical history taking and drug-drug interactions chart review for contraindications for same-day treatment will be conducted. Any participants with suspected decompensated cirrhosis or other comorbidity that may exclude participants from treatment in arm 2 of this study will be referred to a specialist for further review and care.If the POC result is a negative antibody test at 5 min and a positive test at 20 min, blood samples will be collected for confirmatory laboratory RNA testing and additional investigations, and the participant will be told that their test indicates they have been exposed to hepatitis C but may have a current infection. These participants are ineligible for same-day treatment in arm 2, but if their RNA test is subsequently positive, they will be offered treatment as per study procedures of arm 1 of the study but will not count towards the enrolment target.

Participants will be eligible for same-day treatment if they have:

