### Sample size

The primary study aim (aim 1) is to assess if same-day treatment initiation model (arm 2) increases hepatitis C treatment uptake and achievement of SVR, compared with a simplified care model (arm 1). The study is powered to measure the primary outcomes of treatment uptake and cure in arm 1 and arm 2 in a pooled analysis of all three countries. In addition, we will compare retention in care between arm 1 and arm 2, in each country individually. The sample size is presented below (table 3).

**Table 3 T3:** Country and site enrolment and treatment targets

Country	Site	Target enrolment	Target DAA initiation arm 1	Target DAA initiation arm 2
Armenia	Yerevan, National Center for Infectious Diseases	500	58	58
	Shirak, Gyumri Medical Center	164	19	19
	Lori, Vanadzor Medical Center	163	19	19
	Syunik, Kapan Medical Center	163	19	19
	**Total (Armenia**)	**990**	**115**	**115**
Georgia	Tbilisi, Hepa plus	1100	18	18
	Rustavi, New Vector	360	12	12
	Gori, Step to Future	440	42	42
	Xenon	1200	48	48
	**Total (Georgia**)	**3100**	**120**	**120**
Tanzania	Dar es Salaam, Mukikute	522	60	60
	Dar es Salaam, Temeke Regional Referral Hospital MAT Clinic	478	55	55
	**Total (Tanzania**)	**1000**	**115**	**115**
**Total**		**5090**	**350**	**350**

* Sample sizes based on the following antibody and RNA prevalence estimates: Armenia: 39% HCV Ab prevalence, 75% HCV RNA prevalence. Georgia: 58% HCV Ab prevalence, 30% HCV RNA prevalence. Tanzania: 40% HCV Ab prevalence, 75% HCV RNA prevalence.

Ab, antibody; DAA, direct-acting antiviral; HCV, hepatitis C virus.

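### Accuracy of the 5 min read is promised for viraemic versus non-viraemic participants, but RNA is measured only in 20 min reactives, so specificity and NPV computed against RNA describe that subset alone

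*Protocol article*

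**What the plan says.** The Study outcomes section lists sensitivity, specificity, PPV and NPV "of the 5 min read-time OraQuick HCV antibody result in identifying participants with viraemia from those without viraemia". The section on accuracy of the shortened read-time repeats the four measures ("The test performance will be determined by calculating the sensitivity and specificity of the shortened 5 min read-time result") and takes RNA as the comparator: concordance of the 5 min result with the result "from the confirmatory hepatitis C RNA test result will be calculated using data from both arms". Neither section names an analysis set or restricts the measures to antibody-positive participants.

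Who gets an RNA test is fixed in the visit procedures. In arm 1, Visit 1: "If the antibody result is negative, confirmatory testing will not be offered and the participant will exit the study with no further investigations performed". Arm 2, Visit 1 has the same rule and adds the case between the two read times: "If the POC result is a negative antibody test at 5 min and a positive test at 20 min, blood samples will be collected" for RNA testing. In both arms, then, the 20 min result decides who is verified. Everyone reactive by 20 min has RNA measured and nobody else does.

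**The concern.** This is partial verification in a known direction. A participant non-reactive at 20 min was also non-reactive at 5 min, so every unverified participant is a 5 min negative. Leaving them out removes true negatives and, if any of them are viraemic, false negatives. It cannot remove a true or false positive.

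The stated target is wider than the data behind it. A reader who takes the specificity or NPV as applying to all participants tested would be using a figure from antibody-positive people alone, the group in which non-viraemic participants are hardest to separate. One of the two uses described in the Background is to spare RNA tests in people non-reactive at 5 min. Someone who stops reading at 5 min cannot tell a later reactive from a never-reactive, so the negative group for that use contains both. The gap between the two versions also depends on antibody prevalence, so it differs between countries for reasons that have nothing to do with the test.

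**Working it through.** The article gives no target value or sample size for the accuracy outcome, so there is no figure of its own to reproduce. The check builds the expected 2×2 table from Table 3.

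**Inputs from the article (Table 3 and its footnote).** Target enrolment is 990 in Armenia, 3,100 in Georgia and 1,000 in Tanzania. Antibody and RNA prevalences are 39% and 75%, 58% and 30%, and 40% and 75% respectively (for example "Armenia: 39% HCV Ab prevalence, 75% HCV RNA prevalence"). The RNA figures are read as shares of antibody positives. Georgia supports this: 58% × 30% = 17.4%, close to the 18% viraemic prevalence given in its country description.

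**Assumptions, not in the article.**
- *f*, the share of antibody-positive, RNA-negative people reactive by 5 min: 50% to 80%, central value 67%.
- *w*, the viraemic share among 20 min non-reactives: 0% to 2%.
- Sensitivity among RNA-tested participants is 100%, unless stated otherwise.

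**Expected counts.**

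| | Viraemic, Ab+ | RNA−, Ab+ | 20 min non-reactive |
|---|---|---|---|
| Armenia | 289.6 | 96.5 | 603.9 |
| Georgia | 539.4 | 1,258.6 | 1,302.0 |
| Tanzania | 300.0 | 100.0 | 600.0 |
| Pooled | 1,129.0 | 1,455.1 | 2,505.9 |

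The unverified share is 2,505.9 / 5,090 = 49%.

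**Specificity.** In the RNA-tested set it is 1 − f. Over all tested, with non-reactives counted as RNA negative, it is [(1 − f) × 1,455.1 + 2,505.9] / (1,455.1 + 2,505.9).

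- f = 50%: 50%, against (727.6 + 2,505.9) / 3,961.0 = 81.6%.
- f = 67%: 33%, against (480.2 + 2,505.9) / 3,961.0 = 75.4%.
- f = 80%: 20%, against (291.0 + 2,505.9) / 3,961.0 = 70.6%.

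The gap runs from about 32 to about 51 points. It hardly depends on w: at w = 1% the all-tested values are 81.5%, 75.2% and 70.4%.

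By country, with w = 0, the all-tested specificity as f goes from 50% to 80% is 93% to 89% in Armenia, 75% to 61% in Georgia and 93% to 89% in Tanzania. In the RNA-tested set it is 50% to 20% in each.

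**Sensitivity.** In the RNA-tested set it is 100% by assumption. Over all tested it is 1,129.0 / (1,129.0 + w × 2,505.9).

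- w = 0: 100%
- w = 0.5%: 1,129.0 / 1,141.5 = 98.9%
- w = 1%: 1,129.0 / 1,154.1 = 97.8%
- w = 2%: 1,129.0 / 1,179.1 = 95.7%

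**NPV.** In the RNA-tested set only participants turning reactive between 5 and 20 min contribute. As an illustration, take sensitivity 98% in that set, f = 67% and w = 1%. There are then 0.02 × 1,129.0 = 22.6 false negatives and 480.2 true negatives, giving 480.2 / 502.8 = 95.5%. Over all tested it is (480.2 + 0.99 × 2,505.9) / (502.8 + 2,505.9) = 98.4%. For Armenia alone the two values are 85% and 98%.

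**PPV and overtreatment.** Both are defined among 5 min reactives, all of whom are due an RNA test, so neither changes.

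**The case against.** The strongest reply is that the bias is read in. If the analysis set is simply those with a confirmatory RNA result, the measures are valid for 20 min reactives. If it is everyone tested, non-reactives have to be classified somehow, and RNA negative is the natural choice. That stands in part: restricted and labelled, the RNA-verified measures are not biased. But the outcome is worded for participants with and without viraemia, and no restriction is stated, whereas the neighbouring sections on treatment completion and time to treatment do name their denominators.

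A second reply is that denominators belong in the analysis plan, which the article says will be posted on the registration record. That plan could well settle the label. As published, though, the outcome is wider than the data collected for it, and the difference is too large to leave to the reader.

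A third is that presumptive treatment, the study's focus, concerns reactives, for whom PPV and overtreatment matter most. That is correct, and it limits the consequence. A low specificity among antibody positives would also count against arm 2, not for it.

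A reader might go further and infer that sensitivity is certainly biased upward. The article does not support that. It gives no rate of viraemia among 20 min non-reactives, and the only sensitivity it cites for the 20 min read is 100%. Its advice on window periods in arm 1 is for participants who are already antibody positive and have a negative RNA result.

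A reader might also infer a single headline specificity, such as 25%. That would need a 75% share reacting by 5 min, which the article does not give. At a 50% share the pooled PPV would be 1,129.0 / (1,129.0 + 727.6) = 61%, near the 62% cited from the earlier study, though that study was in other populations. Only a range is defensible.

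**Conclusion.** The point holds for specificity and NPV, and conditionally for sensitivity. Computed against RNA, specificity and NPV describe participants reactive by 20 min and not the tested population. That specificity is lower than over all tested participants follows from the testing rules, given that nearly all non-reactives are RNA negative. Its size rests on the Table 3 prevalences, the target enrolment mix and the assumed share reacting by 5 min, and it is at least 30 points pooled across 50% to 80%. For sensitivity there is no error at zero viraemia among non-reactives, and an overstatement of about 1 to 4 points at 0.5% to 2%. This is a secondary outcome, and the figures would be sound if explicitly limited to antibody positives. It should be corrected before analysis, but it does not touch the primary comparison.

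**What to change.** In the Study outcomes section and the section on accuracy of the shortened read-time, label the RNA-verified sensitivity, specificity and NPV as applying among participants reactive at 20 min. Add a second set of these three measures over all participants tested, counting 20 min non-reactives as RNA negative, by country as well as pooled. Accompany it with a bound that varies viraemia among the non-reactives from 0% to 2%. Leave PPV and the overtreated proportion as they are.

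The cost is a change of wording and a few lines of analysis. It needs no further RNA tests, visits or changes to procedures. The one downside is that the bounded sensitivity may look slightly less favourable than the RNA-verified figure.
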